#### T2: Pre-training assessment

Prior to the training, all subjects will undergo an assessment including a series of questionnaires as well as experimental tests measuring implicit associations towards alcohol (IAT) and inhibitory control (GNG, SST). This will take place at the end of the third treatment week. A total of 60 patients (for the EEG substudy) will additionally be assessed with multi-channel EEG while completing the experimental tasks. As the intense confrontation with alcohol pictures may lead to tension and induce craving in patients with AUD, we will monitor our participants’ stress and craving on an 11-point Likert scale (0 = not at all, 10 = very strong) immediately before and after the assessment. In the case of significant stress or craving levels, the medical staff on duty will be contacted and informed.

#### Training (intervention)

During weeks 4 and 5 of the treatment, all patients will undergo six short training sessions according to their allocated training version (Alc-IT (75/25), Alc-IT (50/50) or control group, either in the morning or afternoon). All training sessions will be distributed over 2 weeks, performed in a group setting, and monitored by a member of the study team. At the beginning of the first session, participants undergo a short practice version to confirm that they understood the task. Before and after each training session, stress and craving will be assessed (see also T2). At the end of each training session, the study member will take note of the participants’ reaction time and error rate, with the aim to maintain motivation. In order to assess saliva cortisol concentration for the cortisol substudy, saliva samples of 80 patients of the Suedhang Hospital will be collected before and after the first training.

#### T3: Post-training assessment

One to 4 days after the last training session, patients will undergo the same assessment as in T2 (including questionnaires and experimental tasks). The 60 participants of the EEG substudy again participate in the EEG recording during the experimental tasks. Before and after the measurement, self-reported stress and craving will be assessed (see also T2).

#### Discharge assessment (T4)

Upon discharge from inpatient treatment, psychological parameters are measured again with the questionnaires used at previous time points. At the end of T4, the procedure for the follow-up measurements will be explained.

#### 3-month follow-up (T5)

Three months after discharge, all participants will be contacted by telephone. The primary outcome variables will be assessed in a short telephone interview, and an appointment for the TLFB interview will be arranged if it cannot be carried out at the time of the call. Parallel to this telephone interview, a questionnaire battery will be sent to the patients’ private address.

#### 6- and 12-month follow-up (T6, T7)

Six (T6) and 12 (T7) months after discharge, a similar procedure as in T5 will be performed. At both time points, participants will receive the questionnaire battery by post and will be called by telephone to assess the most significant outcome variables.

#### Procedure to enhance response rates at the follow-up assessments (T5, T6, T7)

To achieve high response rates, a meticulous plan will be pursued for each follow-up assessment: Participants will be contacted by telephone starting 10 days prior to the target day (90, 180 and 365 days after discharge) to announce the upcoming assessment. Should three contact attempts fail, a text message is sent. In case of no response, they are called another seven times, and a set of questionnaires will be sent shortly before the target day. If these questionnaires are not returned within 15 days, they are called another 10 times. If provided, an additional email is sent. This procedure will be repeated if the patient has been reached yet no questionnaires are returned. If it is possible to talk to the participant at any time during the process, the most important primary outcome variables are queried. This entails that at least the most important variables can be collected, even if the participant does not return the questionnaires. As a last resort, a voluntarily provided contact of the participant is called. If none of these attempts succeed, the follow-up assessment will be terminated. Participants receive 20 CHF for each follow-up assessment.

### Procedure for substudies

#### Cortisol substudy

Inclusion and exclusion criteria for the substudy match those of the main study. The first 80 patients who are recruited in the Suedhang Hospital will be additionally asked to participate in the cortisol substudy, which involves collecting a salvia-cortisol sample before and after the first training session.

#### EEG substudy

As this involves more time-consuming measurements at T2 and T3, a two-level recruitment-process will be implemented: Inclusion and exclusion criteria for the substudy match those of the main study. However, recruitment of these participants will additionally depend on their mental capacity, age and gender balance, and their available time considering the clinic’s already demanding agenda. If eligible patients are interested in participating, additional information concerning EEG measurements will be provided, and an additional informed consent for this substudy will be signed. When 20 participants per training version are included in this substudy, the recruitment procedure will be stopped. Patients enrolled in the EEG substudy will receive a monetary compensation of 50 CHF per measurement.

### Procedure for healthy controls

Interested potential participants will receive the participant’s information and informed consent to read. If eligible for the study, a member of the study team will verify the inclusion and exclusion criteria during a screening. If a person is included in the study, written informed consent will be obtained, and the subject will undergo the same experimental tasks (IAT, GNG, SST) and a similar questionnaire battery as the patient sample at T1 (for an overview, see Additional file 5). Questionnaires and behavioral data during tasks will be collected from 30 healthy controls, the same measurement will be collected from another 20 additional healthy controls while an EEG is recorded during the experimental tasks (T2 and T3). Healthy controls without an EEG will receive no monetary compensation, whereas subjects in the EEG group will receive 30 CHF for any EEG-related inconvenience.

## Data collection and statistical analysis

### Questionnaires

Will be assessed by using paper and pencil and will then be entered into SPSS (Version 24.0, IBM SPSS Statistics for Windows, IBM Corp, Armonk, NY, USA). Behavioral data will be collected with E-Prime 2.0 (EP2Pro2.0.10.356, Psychology Software Tools, Inc., Sharpsburg, PA, USA).

### EEG data

Electrophysiological data will be recorded with BrainVision Recorder (Version 2.0, Brain Products GmbH, Gilching, Germany) using 64 active electrodes distributed across the scalp according to the extended 10/10 system. The sampling rate is 500 Hz, online filters are set to 0.016 Hz (high-pass) and 250 Hz (low pass), impedances are kept below 20 kΩ, FCz will serve as on-line reference. Each participant will first undergo a 5-min resting state EEG with alternating epochs of eyes open and eyes closed. Then, the experimental test battery of the T2 and T3 assessment, consisting of a Go-NoGo Task (GNG), an Implicit Association Test (IAT) and a Stop-Signal Task (SST), will be administered while the EEG is still recorded. For details about the tasks, please see section “Experimental tasks.”

### Cortisol data

Saliva samples for *cortisol analyses* will be stored at − 80 °C.

### Statistics

All statistical analyses will be conducted by the members of the study team. The main analyses of the training effect will be carried out after data collection is completed to maintain the study’s double-blind design. All behavioral and questionnaire variables will be tested for normal distribution (Kolmogorov-Smirnov test: *p* > 0.1, for all variables).

#### Main study

Training effects on our primary outcome measures (PDA and HDD at 3-month follow-up) will be assessed with a 2 × 3 analysis of variance (ANOVA) with the factors time point (T1, T5) and training group (Alc-IT (50/50), Alc-IT (75/25) or control). Further, a Cox regression will be computed to predict the effect of the intervention on TFD (at 3-month follow-up).

Training effects on experimental test parameters will be assessed with a 2 × 2 × 3 repeated measures ANOVA with the factors measurement point (T2, T3), time of day (morning, afternoon) and training group (Alc-IT (50/50), Alc-IT (75/25) or control). Where Mauchly’s test of sphericity indicates heterogeneity of covariance, we will verify repeated measures results with Greenhouse-Geisser corrections.

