## Background

Alcohol use disorder (AUD) is a major public health problem which has a substantial impact on patients’ psychological, physiological and social functioning [1–4]. Severe AUD often remains a lifelong condition due to patients’ susceptibility to relapse [5–7]. Despite the development of valuable treatment programs [8, 9], one third of patients relapse within 1 year after treatment, highlighting the need for effective new interventions to be added to these programs.

Current models of substance use disorders (SUDs) are based on neuroscientific research into subcortical alterations (e.g., [10–12]) and psychological investigations on implicit processes [13], and postulate on an imbalance between subcortical, implicit processes and cortical control processes. Briefly, these models assume that automated (subcortical) cue-reactivity is enhanced, thus leading to a strong drive to consume, while the opponent (cortical) executive control is weakened, making it difficult to inhibit this impulse (e.g., [11, 14–16]). The neuroscientific findings that underlie these models include enhanced reactivity to substance-related cues in brain regions related to reward prediction and saliency processing (e.g., nucleus accumbens, amygdala), habits and motivation (dorsal striatum, orbitofrontal cortex) and alterations in brain regions related to inhibitory control (dorsolateral prefrontal cortex, inferior frontal cortex and anterior cingulate cortex) [17, 18]. There is an extensive body of literature indicating that SUD is associated with impaired performance in inhibitory control tasks [19–24]. Until recently, these tasks did not differentiate between inhibition in a substance-related versus neutral context. However, this distinction seems to be clinically relevant, given that the central malfunction leading to relapse is the inability to exert inhibitory control in a substance-related context. Recent studies have suggested that alcohol-related inhibition demands additional neuronal resources in patients with AUD and heavy drinkers [25–28].

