### Power calculation

The intended sample size was calculated with G*Power (Version 3.1.5, Heinrich-Heine-University Duesseldorf, Dusseldorf, Germany). In a-priori analyses (1−β = 0.8, α = 0.05), slightly reduced expected effect sizes were entered compared to earlier studies because of the additional manipulations concerning different training versions and time of training. For the 2 × 3 ANOVA to examine the training effects on the primary outcome measures PDA and HDD (with an expected effect size of f = 0.2 based on earlier studies [32]), a total sample size of *n* = 244 is needed. For the analyses of the training’s effect on TFD (the third primary outcome, estimating a small to medium effect size of w = 0.25 based on earlier studies [37], and df = 3), G*Power indicated a total sample size of *n* = 174 for the Cox regression. For the 2 × 2 × 3 repeated measures ANOVA examining training effects on experimental parameters and also taking into account the effects of time of day of the training (expecting small to medium effects of f = 0.15 and correlations of 0.4 among repeated measures based on earlier studies [107]), the necessary sample size was *n* = 180. Considering the necessary power for all analyses and similar sample sizes in all study arms (82 per intervention group), a total of 246 patients will be recruited.

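### The n = 244 for PDA and HDD is sized for a test with one observation per patient, not for the T1-to-T5 change test that the time-by-group ANOVA amounts to; adjusting T5 for T1 would be more efficient and needs no new data

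*Protocol article*

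**What the plan says.** Under Statistics, Main study, the protocol article assesses training effects on PDA and HDD at 3 months with a 2 × 3 "analysis of variance (ANOVA) with the factors time point (T1, T5) and training group" (three levels). It does not say which term carries the training effect.

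Under Power calculation, the 2 × 3 ANOVA "to examine the training effects on the primary outcome measures PDA and HDD" is sized with "1−β = 0.8, α = 0.05" and "with an expected effect size of f = 0.2 based on earlier studies". The result is that "a total sample size of *n* = 244 is needed"; in the end "a total of 246 patients will be recruited", 82 per training group. No correlation between T1 and T5 is given for this analysis. A correlation of 0.4 appears in the same section, but for the separate repeated measures ANOVA of the experimental tasks at T2 and T3.

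T1 drinking covers the 90 days before detoxification. T5 is 3 months after discharge from an inpatient stay that typically lasts 8 to 12 weeks.

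On distribution, the Statistics section says: "All behavioral and questionnaire variables will be tested for normal distribution".

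**The concern.** With two time points, the group-by-time interaction compares the mean of T5 minus T1 across the three groups. Subtracting T1 removes variance only when T1 predicts T5 well enough; otherwise it adds variance. With equal SDs the break-even correlation is 0.5. In general it is SD(T1) / (2 × SD(T5)). A low correlation is plausible here, because detoxification and a long inpatient treatment lie between the two drinking windows.

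The sample size calculation does not engage with this, since it contains no second measurement. The stated 80% is therefore not shown to be the power of the named primary test. A more efficient use of the same two measurements, adjusting T5 for T1, is not used.

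**Working it through.** **Inputs.** From Power calculation: α = 0.05, power 0.80, f = 0.2, N = 244 needed, 246 recruited, three groups of 82. Assumed, because the article is silent: f = 0.2 is the group effect at T5, all 246 patients have T5 data, equal T1 and T5 SDs (relaxed in step 3), and a T1-T5 correlation ρ shown as a range.

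**1. The plan's figure.** With one observation per patient, the noncentrality is λ = f² × N = 0.04 × 244 = 9.76. The F test with 2 and 241 df has power 80.0%, and 244 is the smallest such N. A six-cell between-subjects layout with 2 numerator df also gives 244 (80.0%). Repeated-measures calculations with f = 0.2 do not:

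| Term | ρ = 0 | ρ = 0.4 | ρ = 0.5 |
|---|---|---|---|
| Group × time, N needed | 124 | 76 | 64 |
| Group main effect, N needed | 124 | 172 | 184 |

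So 244 comes from a calculation without a repeated measure.

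**2. Power at N = 246.** Here f² × N = 0.04 × 246 = 9.84.

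- T5 alone: λ = 9.84, power 80.4%.
- Interaction (T5 − T1): the variance of the difference is 2(1 − ρ) times the T5 variance, so λ = 9.84 / [2(1 − ρ)], df 2 and 243.
- T5 adjusted for T1: the residual variance is (1 − ρ²) times the T5 variance, so λ = 9.84 / (1 − ρ²), df 2 and 242.

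| ρ | λ interaction | Power | λ adjusted | Power |
|---|---|---|---|---|
| 0 | 4.92 | 49% | 9.84 | 80% |
| 0.2 | 6.15 | 59% | 10.25 | 82% |
| 0.3 | 7.03 | 65% | 10.81 | 84% |
| 0.4 | 8.20 | 72% | 11.71 | 87% |
| 0.5 | 9.84 | 80% | 13.12 | 91% |
| 0.6 | 12.30 | 89% | 15.38 | 95% |

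A simulation of 10,000 trials at ρ = 0.4 gave 72.0% and 86.7%.

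If the group main effect were the tested term, it would average in a value taken before randomisation. Then λ = 9.84 / [2(1 + ρ)] = 3.51 at ρ = 0.4, and power is about 37%.

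**3. Unequal SDs.** Let k = SD(T1) / SD(T5). The variance of the difference is (1 + k² − 2ρk) times the T5 variance. At ρ = 0.4:

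- k = 0.75: factor 0.9625, λ = 10.22, power 82%.
- k = 1: factor 1.20, λ = 8.20, power 72%.
- k = 1.25: factor 1.5625, λ = 6.30, power 60%.

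The adjusted analysis does not depend on k and stays at 87%.

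**The case against.** **The meaning of f.** The article does not say that f = 0.2 is the T5 effect. If it were the interaction effect size in repeated-measures terms, power at N = 246 would be 98% at ρ = 0 and above 99.9% at ρ = 0.4. This stands as a reason to make every power figure conditional. But such a calculation would have asked for 124 patients or fewer, not 244, so it does not reconcile the sample size with the named analysis.

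**The correlation.** A reader might infer that power is 72% at the plan's own correlation. The documents do not support that. The 0.4 is given for the T2/T3 tasks, a few weeks apart, and not for drinking before detoxification and after discharge. At 0.5 or above, with equal SDs, nothing is lost against 80%. A T1 SD smaller than the T5 SD would also shrink or remove the loss.

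**Validity.** Randomisation makes the change test a valid comparison of the groups. No bias follows from choosing it.

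**Distribution.** A reader might also infer that PDA and HDD are bound to fail the normality check, because the Background says "one third of patients relapse within" 1 year after treatment. That is general background with relapse undefined; it does not fix the share of patients at PDA 100% and HDD 0 at 3 months. Many values may sit there, but the article does not establish how many. What follows a failed check may be set out in a fuller document.

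**Conclusion.** The point holds as a mismatch and an efficiency loss. The sample size calculation describes a test with one observation per patient, while the analysis section describes a repeated-measures ANOVA whose natural test is on the T1-to-T5 change. Under the stated assumptions, the interaction test lies between 49% and 80% power for correlations from 0 to 0.5, and above 80% beyond that. The adjusted analysis lies between 80% and 91% over the same range and is the more powerful of the two at every correlation tabulated. The exact shortfall cannot be fixed from the article, because it depends on an unstated correlation, an unstated meaning of f and unstated SDs; any loss to follow-up lowers all the figures. The preference for adjustment does not hinge on these values. This should be fixed, but it does not threaten the validity of the trial.

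**What to change.** Replace the 2 × 3 ANOVA for PDA and HDD by an ANCOVA of the T5 value on training group (three levels), with the T1 value of the same outcome as covariate. Name the 2-df group effect as the test. Restate the power for that test, giving the assumed T1-T5 correlation and saying that f refers to the group effect at T5.

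Because many T5 values may lie at PDA 100% and HDD 0, a permutation p-value for the ANCOVA group effect can accompany the model, with the adjusted mean difference reported.

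The cost is a sentence or two in the analysis section and one recomputed power figure. The T1 interview already yields PDA and HDD, and no extra patients or visits are needed. The article places the main analyses after data collection is complete, so the change should be recorded before the training groups are unblinded.

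### The T1/T5 ANOVA for PDA and HDD uses only patients with a 3-month value, so drinking-related loss to follow-up could bias the training contrast in either direction

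*Protocol article*

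**What the plan says.** In the protocol article, the Main study part of the Statistics section analyses PDA and HDD at 3 months by a 2 × 3 ANOVA "with the factors time point (T1, T5) and training group". Only T1 and T5 enter. TFD is handled separately by Cox regression.

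The section on enhancing follow-up response plans for patients who are hard to reach. It sets out up to three, then seven, then ten telephone attempts, with a text message, an e-mail, a payment per assessment and, as a last resort, a contact person named by the patient. Key primary outcomes are asked whenever the patient is on the telephone, even if no questionnaire comes back. It then accepts that some assessments will fail: "If none of these attempts succeed, the follow-up assessment will be terminated".

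Drinking data are also planned after T5. At 6 and 12 months patients "will be called by telephone to assess the most significant outcome variables", and the Study aim lists PDA, HDD and TFD as distal outcomes at 3, 6 and 12 months.

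The Power calculation states for PDA and HDD that "a total sample size of *n* = 244 is needed", and plans "similar sample sizes in all study arms (82 per intervention group), a total of 246 patients will be recruited".

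**The concern.** A patient with no T5 value has no second time point and cannot enter a T1/T5 ANOVA unless that value is imputed. As named, the model therefore leaves that patient out, together with any drinking data obtained at T6 or T7. The resulting estimate is unbiased only if being reached at 3 months is unrelated to drinking. After inpatient treatment for alcohol use disorder, with drinking itself as the outcome, that is a demanding assumption.

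Two results are at stake: the level of abstinence reported in each arm, and the training contrast on two of the three primary outcomes. The concern is with the model the article chose. It is not that an imputation rule or a sensitivity analysis is absent, since those may stand in an analysis plan that is not shown.

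**Working it through.** **1. The plan's own figure.** Inputs from the Power calculation: "In a-priori analyses (1−β = 0.8, α = 0.05" and "with an expected effect size of f = 0.2 based on earlier studies". A fixed-effects ANOVA with numerator df = 2 and noncentrality λ = N·f² = N × 0.04 reaches 80% power at N = 244, so the stated figure reproduces exactly. Recruitment of 246 leaves 246 − 244 = 2 patients (0.8%), attributed to power for all analyses and similar arm sizes rather than to attrition. In its own terms the calculation presumes nearly complete T5 data. At assumed overall losses of 10%, 20% and 30% (N = 221, 197, 172), the same formula gives power 0.76, 0.70 and 0.64.

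**2. Selective loss: inputs.**
- Relapse proportions p_C (control) and p_T (training) at 3 months: assumed. The only relapse figure in the article is in the Background ("one third of patients relapse within 1 year after treatment"), and it is a 1-year figure.
- Proportion reached at T5: r_N for non-relapsed and r_R for relapsed patients. Assumed, because the article gives no retention rates.
- Mean PDA of 95 if not relapsed and 50 if relapsed: assumed. These set the levels but not the ratio below.

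**3. Formulas, with response equal across arms.** The proportion of an arm that is reached is D = p·r_R + (1 − p)·r_N. The relapsed share among those reached is q = p·r_R / D. Mean PDA is 95 − 45p in truth and 95 − 45q as observed. Then

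observed contrast / true contrast = (q_C − q_T)/(p_C − p_T) = r_R·r_N / (D_C·D_T).

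**4. Results with r_N = 0.90 and r_R = 0.60 (r_R·r_N = 0.54).**

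| Relapse, control / training | D_C | D_T | Observed / true contrast |
|---|---|---|---|
| 33% / 20% | 0.801 | 0.840 | 0.54 / 0.673 = 0.80 |
| 50% / 33% | 0.750 | 0.801 | 0.54 / 0.601 = 0.90 |
| 70% / 55% | 0.690 | 0.735 | 0.54 / 0.507 = 1.06 |
| 80% / 65% | 0.660 | 0.705 | 0.54 / 0.465 = 1.16 |

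At 33%/20% the true PDA means are 80.15 and 86.00 (difference 5.85). The observed means are 83.88 and 88.57 (difference 4.70). Abstinence is overstated by 3.7 and 2.6 points. At 80%/65% the true means are 59.00 and 65.75 (difference 6.75) and the observed means 62.27 and 70.11 (difference 7.83). Abstinence is again overstated in both arms, but the contrast is now too large.

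Milder selection, r_R = 0.75 at 33%/20%, gives 0.675 / (0.8505 × 0.87) = 0.91.

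**5. Response that differs by arm (33%/20% relapse, r_N = 0.90).**
- Relapsed patients reached 75% in control, 50% in training: q_C = 0.2910, q_T = 0.1220, ratio 0.1690 / 0.13 = 1.30.
- Reversed (50% and 75%): q_C = 0.2148, q_T = 0.1724, ratio 0.0424 / 0.13 = 0.33.
- No true effect (33% in both arms), 75% versus 50%: 45 × (0.2910 − 0.2148) = 3.4 PDA points of spurious difference.

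The overstatement of abstinence needs only that relapsed patients are reached less often. The direction of bias in the contrast depends on how common relapse is and on whether response differs by arm.

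**The case against.** **The article never states a complete-case analysis.** It names a model and its factors. An ANOVA can be run on imputed values, and imputation rules and sensitivity or tipping-point analyses are commonly left to the analysis plan. This stands: their absence from a condensed article is no finding. The choice of model remains open to comment, because a T1/T5 model leaves later drinking data out by construction.

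**The loss may be small.** Asking primary outcomes at any telephone contact, and turning to a contact person, bear directly on the assumed response of relapsed patients. This also stands in part. The measures reduce loss, but the section itself provides for assessments that end without data, and it does not say that the contact person supplies drinking data.

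**No document says that relapsed patients are harder to reach.** Correct. It is an assumption here, plausible but not documented.

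**Later data cannot stand in for T5.** Under Alcohol use disorder and other substance use, the TLFB covers 90 days and its interview is named for T1 and T5 only. T6 and T7 therefore inform the missing window only indirectly, which limits what the fix can achieve.

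A reader might infer that the training effect will shrink. The documents do not support that: shrinkage follows only when response is equal across arms and relapse is not too common, and the one-third figure is not a 3-month rate. A reader might also infer a raised false-positive rate. That needs response that differs by arm, and the article describes blinded patients and staff, trainings of equal length and one follow-up procedure for all.

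**Conclusion.** The point holds in conditional form. The stated primary model for PDA and HDD uses only patients with a T5 value, although non-response is foreseen and the same outcomes are planned at T6 and T7. If relapsed patients are reached less often, abstinence is overstated and the training contrast can be biased in either direction. Under assumed 90%/60% response, equal across arms, the observed contrast is about 80% of the true one at 33% versus 20% relapse and about 116% at 80% versus 65%. Every response rate and 3-month relapse rate in that illustration is assumed, so it shows possible size and direction and forecasts nothing.

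The power figures should not be read as proof that the trial is underpowered. They apply only to the fixed-effects calculation the article appears to have used. A group-by-time interaction with f = 0.2 would need 124, 64 or 40 patients at a correlation of 0, 0.5 or 0.7 between the two time points. The reason to change the model is possible bias and unused data. The change is worth making and cheap, but the documents do not show that the stated analysis would mislead.

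**What to change.** In the Main study part of the Statistics section, replace the T1/T5 ANOVA for PDA and HDD by a likelihood-based repeated-measures mixed model on all randomised patients. Take T5, T6 and T7 as the outcomes, include T1 in the model, and read the training contrast at T5, so that the 3-month question is unchanged. A patient who misses T5 but is reached later then contributes.

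The cost is a few sentences and slightly more analysis work, with no new patients or assessments. The limits should be stated with it. The model assumes missing at random given the observed T1, T6 and T7 values. It gains almost nothing from patients who are never reached again. Because T6 and T7 inform the missing 3-month window only indirectly, it removes only part of any bias. How much it removes has not been worked out here.
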